While the body of evidence for the effectiveness of PBT for falls prevention is growing, there are other factors to consider [8, 32, 34–36, 39–41]. The perturbations applied in these studies are of such a magnitude that they may not be acceptable to all older adults. Even the most effective interventions are likely to fail if they are not acceptable to the target population. Therefore, the literature recommends combining quantitative and qualitative methods to assess both the effectiveness and acceptability of a new intervention [42]. In this study, we will assess the acceptability of our training protocol through semi-structured interviews, utilizing the definition and theoretical framework of acceptability (TFA) described by Sekhon et al. [43].

This study protocol describes a mixed-methods study combining an outcome-assessor blinded randomized controlled trial (RCT), using two parallel groups (1:1) and a superiority design, with qualitative research concerning the acceptability of the intervention. The primary aim is to determine the effect of our three-session PBT intervention on balance control measured with the Mini-BESTest in community-dwelling older adults (≥65 years) who visit the outpatient clinic after a fall, in comparison to usual care. Secondly, we aim to determine the effect on real-life falls incidence during a 6 months follow-up period. We will also evaluate the effect on fear of falling measured with the Falls Efficacy Scale International (FES-I). A long-term follow-up evaluation will take place at 2 years post-baseline when each subjects’ electronic patient record (EPR) will be checked with the aim of investigating the long-term effect of PBT on injurious falls.

Lastly, we aim to determine the acceptability of our three-session PBT protocol through semi-structured qualitative interviews in a sub-group of the intervention group in this study.

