### Subjects

Community-dwelling older adults (65+) who have experienced a fall in the past 3 months and visit the MUMC+ outpatient clinic will be approached to participate in this study. To ensure that our sample includes only older adults at increased risk for falling, persons who fell during exercise activities (i.e. cycling) or due to actions of a third party, will be excluded. Similarly, persons using medication that is known to increase the fall risk will be excluded from this study. For a full description of the eligibility criteria, see Table 1.

**Table 1 Tab1:** Full eligibility criteria

Inclusion criteria	Exclusion criteria
Age ≥ 65 years	Diagnosed with osteoporosis
Community-dwelling	Recent fracture or severe contusion of the lower extremities, back or shoulders (in consultation with medical doctor)
Able to walk without a walking aid for ≥15 min	Any disease or disorder that may influence the safety of training (e.g. severe cardiopulmonary disease)
Recently having experienced a fall (≤3 months ago)	Falls caused by actions of third parties or during exercise activities
Having visited the MUMC+ outpatient clinic after their fall incident	Uncorrected vision problems
	Falls due to syncope
	Use of medication known to increase fall risk (antidepressants, benzodiazepines, sedatives, hypnotics, antipsychotics) [44]
	Use of painkillers that can decrease responsiveness (e.g. morphine, oxycodone) [44]
	Inability to provide written informed consent and communicate in Dutch
	Inability to follow instructions due to cognitive problems

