### Timeline

The first study visit for subjects consists of two parts; t_− 1_ is where subjects make their final decision on participating in the study, informed consent is obtained and the eligibility criteria are checked. If a subject meets all eligibility criteria, this visit is combined with t_0_. At t_0_, baseline measurements are performed by the outcome assessor, which will be blinded to treatment allocation. Subjects are explicitly instructed to hide their treatment allocation from this researcher. If the treatment allocation of an individual subject is revealed to the outcome assessor, a second blinded outcome assessor will take over the remaining measurements. After baseline measurements, the subject is randomized to the control- or intervention group by the same researcher that enrolled the subject in the study. For subjects in the intervention group, this visit is followed by three training sessions in 3 weeks. Both groups have their t_1_ visit at 4 weeks post-baseline, and a t_2_ visit 3 months after that, t_2_ being the last study visit for subjects. From t_0_ on, all subjects will fill in falls calendars until 6 months after t_1_. A final check of the EPR at t_3_, 2 years post baseline, concludes data collection for this study. An overview of the study timeline is presented in Table 2.

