#### Retrospective falls incidence

At baseline, the number and circumstances of falls during the past year of each subject will be recorded. A fall is defined as ‘an event which results in a person coming to rest inadvertently on the ground or floor or lower level’ [50]. We will use an adapted version of the ‘falls history questionnaire’ as presented in the book *‘Falls in older people: risk factors and strategies for prevention’* [51]. This questionnaire records if a fall has occurred in the previous period (12 months), where it has happened, what the perceived cause was, and if and what kind of injuries were sustained. The outcome assessor will fill in this questionnaire together with the subject to make sure that the recorded data is as comprehensive and clear as possible.

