#### Prospective falls incidence

From the moment of inclusion, the prospective falls incidence of each subject will be monitored for up to 8 months (the potential training period + 6 months) post baseline. The prospective falls incidence will be monitored with falls diaries and questionnaires. The falls diary is a calendar that the subject will fill in at the end of each day. They are instructed to put an ‘X’ if they did not fall that day, or a number representing the number of times they fell during that day. At the end of each month, subjects will fill in the falls history questionnaire about that particular month, and send this back to the researchers in pre-addressed and pre-paid envelopes. If a fall incident is reported, the researcher will follow this up with a short phone call to elaborate on the circumstances and consequences of this fall. If a calendar has not been returned within 10 working days after the end of the month, the researcher will remind the subject with a phone call. A final follow-up will take place at 2 years post-baseline, where the researcher will check each patients’ EPR, to see if there were any more hospital visits due to injurious falls.

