### Statistical analysis

Data will be analyzed using the Statistical Package for the Social Sciences (SPSS) version 23.0 (SPSS, Chicago, Ill., USA). Descriptive statistics will be used to explore the data and will be presented in tables and figures. Data will be displayed as mean and standard deviation (SD) or as median and interquartile range (IQR), depending on normal distribution of the data. Categorical data will be summarized by frequency (n) or percentage (%). Data will be analyzed on an intention-to-treat basis; missing data will be imputed using multiple imputation. In all statistical analyses, statistical significance will be set at *p* < 0.05. Data-analysis will be performed by a researcher who is blinded to the group allocation.

Primary analysis will test whether there is a significant difference in balance, as measured with the Mini-BESTest, between the control- and intervention groups at T_1_. This will be analyzed using multiple linear regression. Based on the randomization, no between-group differences in variables are expected. However, if there are differences at baseline (based on qualitative appraisal of the baseline table), these factors will be entered into the model. The secondary study parameter ‘fear of falling’ will be analyzed using the same method. The incidence of falls will be analyzed using generalized linear regression with a link function appropriate for the number of falls, using the mean number of retrospective and prospective falls per person-time unit.

A longitudinal analysis will be performed as a secondary, more explorative analysis of balance (Mini-BESTest) and fear of falling (FES-I) over time. A linear mixed effect model will be used to assess the treatment effects, since this model uses all available data, accounts for missing data using a likelihood based method - where missingness at random (MAR) is assumed - and takes the correlation between repeated measurements within a subject into account. The fixed part of the model consists of time, time*treatment, and other covariates that are related to the outcome (power gain) and/or to the missingness (to ensure MAR). The treatment factor, indicating the different treatment groups, is not included, since no group effect is assumed at baseline due to randomization. As for the random part of the model, an unstructured covariance structure is assumed for the repeated measures.

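### As worded, the falls analysis mixes pre-randomisation falls into the incidence measure, which would pull the rate ratio toward 1

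*Protocol article*

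**What the plan says.** **Aim.** The Background states the second aim as follows: "we aim to determine the effect on real-life falls incidence during a 6 months follow-up period".

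**Model.** Under Statistical analysis: "The incidence of falls will be analyzed using generalized linear regression with a link function appropriate for the number of falls", and this is done "using the mean number of retrospective and prospective falls per person-time unit". The section states no period term, no time-by-treatment term and no prior-falls covariate for this model. The next paragraph does specify time and time-by-treatment, but only for Mini-BESTest and FES-I.

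**Retrospective falls.** Under Retrospective falls incidence: "At baseline, the number and circumstances of falls during the past year of each subject will be recorded". The Timeline section puts allocation afterwards: "After baseline measurements, the subject is randomized to the control- or intervention group". Table 1 requires a fall within the 3 months before entry, so nobody has a retrospective count of zero. The past-year count (1 versus 2 or more) is also a stratification factor.

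**Prospective falls.** These have their own heading and a different recording method (daily calendars). The window is described in three ways: 6 months in the Background, "all subjects will fill in falls calendars until 6 months after t_1" in the Timeline (with t1 at 4 weeks, so about 7 months from baseline), and "monitored for up to 8 months (the potential training period + 6 months) post baseline" under Prospective falls incidence.

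**The concern.** The treatment effect on falls can show only in falls that happen after randomisation. Putting the preceding year into the same rate adds events that are equal in expectation in the two arms and cannot respond to training. The prior year is the longer of the two windows, eligibility guarantees it at least one event per person, and stratification balances it between arms. All of this moves the ratio toward 1.

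What is at stake is the estimate for the second aim. The Weaknesses section concedes that falls may matter more to older adults than the primary outcome. A diluted ratio near 1 could be taken as evidence that the training does not prevent falls, when the near-null result comes partly from how the outcome was built.

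**Working it through.** The protocol states no falls rate, event count or power for falls, so there is no figure to reproduce. The check is how far a true ratio moves if the sentence is followed literally.

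**Inputs from the document**
- Retrospective window: 12 months.
- Prospective window *m*: 7 months (Timeline), with 6 and 8 as alternatives.
- True ratios RR: 0.71 (pooled studies of perturbation training) and 0.50 (the single-session study), both cited in the Background.

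**Assumption**
- *k* is the retrospective rate divided by the prospective control rate. The document does not give it; 0.5, 1 and 2 are used.

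**Formula.** Let *p* be the monthly control rate in follow-up. Expected falls per subject are 12*kp* + *mp* in the control arm and 12*kp* + RR × *mp* in the intervention arm. Person-time is the same in both arms and cancels, so:

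apparent ratio = (12*k* + *m* × RR) / (12*k* + *m*)

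**Results, *m* = 7**

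| *k* | true 0.71 | true 0.50 |
|---|---|---|
| 0.5 | (6 + 4.97)/13 = 0.844 | (6 + 3.5)/13 = 0.731 |
| 1 | (12 + 4.97)/19 = 0.893 | (12 + 3.5)/19 = 0.816 |
| 2 | (24 + 4.97)/31 = 0.9345 | (24 + 3.5)/31 = 0.887 |

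At *k* = 1 the share of the reduction that is lost is 12/19 = 63%.

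**Window.** At *k* = 1, a true 0.71 gives (12 + 4.26)/18 = 0.903 for *m* = 6 and (12 + 5.68)/20 = 0.884 for *m* = 8. The choice of window moves the result by about 0.01.

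**Absolute rates.** Eligibility sets a floor of 1 prior fall per year. Assuming 1.0 to 2.0 prior falls per year and 0.5 to 2.0 control falls per year in follow-up, with *m* = 7, a true 0.71 appears as 0.84 to 0.96 and a true 0.50 as 0.73 to 0.94.

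**Direction.** For any *k* > 0 and RR < 1, the formula gives a value strictly between RR and 1. Only the size depends on the assumptions.

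**Simulation.** 40 per arm, 1,500 runs, Poisson regression with estimated overdispersion, two-sided 5%. Assumed: on average 1.5 prior falls per year (at least 1 each), 1.0 control fall per year over 7 months, and gamma-distributed differences between subjects with variance 1.

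| True ratio | Pooled: median ratio, rejection rate | Prospective only: median ratio, rejection rate |
|---|---|---|
| 1 | 1.01, 5% | 1.00, 5% |
| 0.71 | 0.91, 10% | 0.70, 14% |
| 0.50 | 0.86, 16% | 0.50, 35% |

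The prospective count adjusted for log prior falls gives median ratios of 0.71 and 0.50 for the last two rows.

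**The case against.** **The sentence may not mean pooling.** This is the strongest reply. The wording does not say that the two kinds of falls are added. It can be read as two rates, each put on person-time because the windows differ, or as a pre/post contrast by group. The separate outcome headings and the stated aim favour two quantities, and the Sample size section shows the authors treating a baseline score as a predictor for the primary outcome. None of these readings dilutes the effect. This stands as a reason not to assert that pooling is intended. It does not clear the text: none of those alternatives is written for the falls model, and an analyst following the sentence could pool.

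**The weighting is undefined.** This also stands. Even under a combined reading, a simple mean of the two rates at equal rates gives (1 + 0.71)/2 = 0.855 rather than 0.893. The figures above are therefore conditional on pooling.

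**Falls are secondary and unpowered.** True, and stated under Weaknesses. At a true 0.71 the simulated power is low either way (10% against 14%).

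Two stronger readings are tempting, and the document does not support them:
- *A reader might infer that a before-after comparison would be biased by regression to the mean, because everyone enters after a recent fall.* Both arms enter that way and randomisation is stratified on prior falls, so the decline is equal in expectation and cancels between arms. It would mislead only within one arm, and no such comparison is proposed.
- *A reader might infer that a mean rate throws away the count distribution.* The same sentence calls for a link suited to the number of falls, which points to a count model with person-time as exposure.

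**Conclusion.** The point holds in a limited form. As worded, the falls measure draws on falls from before randomisation, gives them no role as covariate or separate period, and so conflicts with the stated aim. Taken literally, it attenuates the rate ratio toward 1.

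The size is conditional on pooled person-time, a 7-month prospective window and assumed rates. With the retrospective rate half to twice the prospective control rate, a true 0.71 would appear as about 0.84 to 0.93 (0.89 at equal rates). A true 0.50 would appear as about 0.82 at equal rates.

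The harm is an attenuated estimate and lost power. It is not a false-positive problem: simulated type I error stays at about 5%. The primary Mini-BESTest analysis is untouched. A reader might infer that the falls result is certain to be diluted, but the text does not establish that, because the authors may have meant something harmless. For a secondary, openly unpowered outcome this is a correction to make before the falls analysis, not a threat to the trial's main conclusion.

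**What to change.** Replace the clause on retrospective and prospective falls with a definition along these lines:

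- The outcome is each subject's count of falls after randomisation.
- It is analysed with the planned count model (for example negative binomial), with treatment as a factor and log follow-up time as offset.
- Falls in the year before baseline enter only as a baseline covariate, in keeping with their use as a stratification factor, and are otherwise reported descriptively.

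At the same time, fix one prospective window across the Background, Timeline and Prospective falls incidence sections. Say when it starts, so that it is clear whether falls between t0 and t1 count.

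The cost is one sentence in the analysis section plus aligned wording on the window. All the data are already being collected, and the sample size does not change.

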### Outcomes

#### Balance control (main outcome)

The main outcome in this study is balance control, which will be measured with the Mini Balance Evaluation Systems Test (Mini-BESTest). The Mini-BESTest has been identified as the most comprehensive measurement tool to assess balance in community-dwelling older adults [46]. It measures balance in four categories: proactive balance, reactive balance, sensory orientation and dynamic gait. Each of the 14 tasks is scored on a three-point scale, with a total score that can range from 0 to 28 points. A higher score corresponds with better balance control. Proactive balance is tested using a sit-to-stand transfer where the subject has to try not to use their hands, standing on tiptoes, and standing on one leg. Reactive balance is tested with therapist-applied lean-and-release perturbations in the forward, backward and sideways directions. Sensory orientation is tested by standing with feet together, standing with feet together and eyes closed on a foam surface, and standing on a slope with eyes closed. Dynamic gait is tested with five tasks; suddenly changing gait speed, walking while turning the head left and right, walking and turning, stepping over an obstacle while walking, and Timed Up and Go performance. The Mini-BESTest has good psychometric properties [47, 48]. Cut-off values indicating increased fall risk for the Mini-BESTest are age dependent; ≤25 points for people 60 to 69 year of age, ≤23 points for 70 to 79 years, ≤22 points for 80 to 89 years and ≤ 17 points for 90 years and older [49]. The minimal detectable change on the Mini-BESTest is 3.5 points and the minimal important change is 4 points [47]. Balance control will be measured at baseline, T_1_ and T_2_.

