### Sample size

Sample size was calculated in G*power 3.1.9.2 and was based on the primary outcome of this study, difference between means on balance measured with the Mini-BESTest at T_1_. The effect size *d* (0.61) was calculated based on values from an article with a similar study population and an intervention aimed at improving dynamic balance control [56]. We assumed that our control group would remain stable as they receive no extra training aimed at balance improvement. Sample size was based on a one-tailed independent samples t-test, an α of 0.05, power (1-β) of 0.80 and allocation ratio of 1. This results in a required sample size of *n* = 72. Accounting for an expected loss to follow-up of 10%, the final sample size is *n* = 80. Sample size was estimated conservatively, making no assumptions about the correlation between predictors (group allocation and baseline score) added into the model and the outcome variable.

For the purpose of investigating the acceptability of the PBT protocol, a sub-sample from the intervention group will be included. The sample size will be based on the concept of theoretical saturation as described by Glaser & Strauss [57]. If there are two consecutive interviews that provide no new information, no new interviews will be planned. We expect to include approximately 15 subjects for the interviews.

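### Longitudinal model: omitting treatment while keeping time*treatment does not impose the intended equal baseline means if the terms are entered as factors in SPSS

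*Protocol article*

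**What the plan says.** All of this is in the Protocol article, mostly under Statistical analysis.

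- Software: "Data will be analyzed using the Statistical Package for the Social Sciences (SPSS) version 23.0".
- Role of the model: "A longitudinal analysis will be performed as a secondary, more explorative analysis of balance (Mini-BESTest) and fear of falling (FES-I) over time".
- Fixed effects: "The fixed part of the model consists of time, time*treatment, and other covariates".
- Reason for leaving out the main effect: "The treatment factor, indicating the different treatment groups, is not included, since no group effect is assumed at baseline due to randomization".
- Covariance: "an unstructured covariance structure is assumed for the repeated measures".
- Occasions (Balance control section): "Balance control will be measured at baseline, T_1_ and T_2". The Fear of falling section gives the same three occasions for the FES-I.

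The intent is clear: one common baseline mean, with treatment effects only after baseline. The article does not say whether time and treatment enter as factors or as constructed indicators, or which contrast will be reported as the treatment effect. The primary analysis is a separate multiple linear regression at T1, and fear of falling is analysed at T1 in the same way.

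**The concern.** The article lists the model terms and gives a reason for the list. The reason works only if removing the treatment term removes the baseline group difference. When time is a factor it does not, because the interaction then supplies one group contrast per visit, baseline included. Calling treatment a factor and naming SPSS make this form of entry plausible.

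The result would be a different model from the one the text describes. It would make no use of the equal-baseline assumption, would be less precise, and would leave the follow-up contrasts exposed to chance baseline imbalance. This is also the only analysis the article describes for balance and fear of falling at T2, so it bears on whether any effect is retained.

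**Working it through.** The point rests on no figure stated in the plan, so there is none to reproduce. The only number borrowed from Sample size is 36 per arm (72/2). It sets the absolute standard errors but cancels from every ratio below.

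**1. What the listed terms span.** There are 3 visits x 2 arms = 6 cell means. Let t = 0, 1, 2 for baseline, T1, T2, and g = 0, 1 for control and intervention.

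- Both terms as factors: E(Y) = mu + tau_t + gamma_tg. The baseline difference is gamma_01 - gamma_00, which is free. Design-matrix rank: 6.
- Full factorial (time + treatment + time*treatment): rank 6. Stacking the two matrices still gives rank 6, so they span the same space. Omitting treatment only relabels the parameters.
- Factor time with treatment as a 0/1 covariate: E(Y) = mu + tau_t + delta_t g, with delta_0 free. Rank 6 again.
- Intended model: the same with delta_0 = 0, so treatment appears only at T1 and T2. Rank 5, and the fitted baseline difference is always 0.

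As a check, a one-unit baseline difference put into the cell means is fitted as 1.0 by each rank-6 version and as 0 by the rank-5 version.

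**2. What the T1 estimate becomes.** With six free means and complete data, the fitted means are the observed cell means whatever the covariance. The within-T1 treatment estimate is therefore the raw T1 difference, D1. With equal SDs and baseline-T1 correlation r, and D0 the chance baseline difference:

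- slope of D1 on D0 = Cov(D1, D0)/Var(D0) = r;
- Var(D1) = 2/n, in SD-squared units with n per arm.

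The intended model gives D1 - r D0, whose variance is (2/n)(1 + r^2 - 2r^2) = (2/n)(1 - r^2). The variance ratio is therefore 1/(1 - r^2). The same formula holds at T2 with the baseline-T2 correlation.

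**3. Numbers.** Assumptions: n = 36 per arm, SD = 1, no covariates, complete data. The SE under factor entry is sqrt(2/36) = 0.236 throughout. The values of r are assumed, as the protocol gives none.

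| r | 1 - r^2 | Intended SE | Variance ratio | SE ratio |
|---|---|---|---|---|
| 0.3 | 0.91 | 0.225 | 1.10 | 1.05 |
| 0.5 | 0.75 | 0.204 | 1.33 | 1.15 |
| 0.6 | 0.64 | 0.189 | 1.56 | 1.25 |
| 0.7 | 0.51 | 0.168 | 1.96 | 1.40 |

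**4. Simulation check.** There were 1,500 trials at each of r = 0.3, 0.5 and 0.7, with 36 per arm, complete data, equal correlations, estimated unstructured covariance and an effect of 0.61 SD at both follow-ups.

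- The factor-entry T1 estimate equalled the raw T1 difference to about 1e-15.
- Its slope on baseline imbalance was 0.26, 0.52 and 0.69. The intended model's slope was -0.04, 0.02 and -0.01.
- The SD of the T1 estimate was 0.229, 0.236 and 0.238 under factor entry, against 0.221, 0.202 and 0.177 under the intended model.
- The variance of the intended model relative to factor entry was 0.93, 0.74 and 0.56, against 0.91, 0.75 and 0.51 from the formula. The formula treats the covariance as known. At r = 0.7 the simulated gap is somewhat smaller (1/0.56 = 1.8 rather than 1.96).
- The intended model's T1 estimate agreed with a baseline-adjusted regression to four decimals.

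**The case against.** The strongest reply is that the article never fixes the coding. Its term list, read with the stated reason, can be taken as shorthand for the common-baseline model, and indicator coding is detail that an article may leave to an analysis plan. Part of this stands: if the analyst already uses post-baseline indicators, only the wording needs changing. It does not dispose of the point, because the article does more than leave coding open. It gives a term list and says why that list produces equal baselines, and under ordinary factor entry in the named software it does not.

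A reader might infer more than the text supports:

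- **That the plan returns an effect unadjusted for baseline.** The article does not name the contrast. The statement is exact only for the within-visit contrast with complete data, and Sample size expects 10% loss. A difference-in-change contrast from the same fit does use baseline, though less efficiently than the intended model (simulated SDs 0.283, 0.231 and 0.190 against 0.221, 0.202 and 0.177 at r = 0.3, 0.5 and 0.7).
- **That baseline imbalance passes in full into the follow-up effects, or biases them.** It passes with a slope of about r, and randomisation keeps the estimate unbiased.
- **That time might be linear, forcing the effect to grow.** Numeric time with 0 at baseline would give equal baselines and an effect proportional to time, but nothing in the article says time is linear. The size would also depend on which timing of T2 is used: 17/4 = 4.25 times the T1 effect if T2 is three months after T1 (Timeline), or about 13/4 = 3.25 if it is three months after baseline (Abstract). This is not part of the finding.

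The size is also uncertain. At r = 0.3 the loss is small, and the planned covariates related to outcome could narrow the gap further.

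**Conclusion.** The specification is wrong as written, in a limited sense: the equal-baseline property that the article claims does not follow from the terms it lists when time is a factor and treatment is a factor or a 0/1 variable. The finding is conditional on that literal entry, which is plausible but not stated.

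The consequence is lost precision and exposure to chance imbalance, not bias. The T1 standard error is about 5% to 40% larger over r = 0.3 to 0.7, assuming complete data, equal SDs and no covariates. A reader might take this as a threat to the main result, but the documents do not support that: the primary T1 regression is a separate analysis, and this model is labelled secondary and exploratory. It should still be corrected, because it is the only described analysis of balance and fear of falling at T2.

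**What to change.** State in Statistical analysis that:

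- time is categorical (baseline, T1, T2);
- treatment enters only through two indicators, treatment x T1 and treatment x T2, both coded 0 for every subject at baseline, so that the arms share one baseline mean;
- the covariance stays unstructured;
- the two indicator coefficients are reported as the treatment effects at T1 and T2;
- the baseline score of the same outcome is not also entered as a covariate, since it is already one of the modelled outcomes.

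The cost is two constructed variables and one added sentence. Sample size, data collection and the primary analysis do not change.
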